### Development of the measurement tool

Data will be measured by a 46-item researcher-made questionnaire. This instrument has been created by reviewing literature on milk donation and previous studies on TPB and consists of seven sections as described in Table 2.

**Table 2 Tab2:** Theory of planned behavior-based survey questions

Sections	Example of questions	Scale
Sociodemographic and perinatal characteristics	Age, education, milk and blood donation history, breastfeeding history, economic status, parity, mode of delivery, the gestational age, sex and age of infant, awareness of HMBs and the source of information of HMBs	-
Knowledge of DHM and HMBs	“What is a human milk bank?” “What is the best alternative to mothers’ own milk for feeding premature babies?” “What effects does pasteurization have on donor milk?” “In the hospital, which babies receive donor milk?” “Who is eligible to donate their breast milk?” “How is donor milk stored in the hospital?” “How long can donated breast milk be stored in the hospital?” “What effects has pasteurized donor milk on premature babies?” “What should mothers do before donating their breast milk?” “What are the characteristics of informal breast milk sharing in the community?”	Multiple-choice questions
Attitude toward DHM and HMBs	“It is pleasant for me to donate breast milk” “Feeding premature babies with donor milk is better than formula” “Donor milk can reduce the stress of mothers who can’t feed their babies with their own breast milk” “By donating breast milk to a milk bank, I can save a baby’s life” “Donating breast milk to the milk bank can reduce the incidence of serious gastrointestinal disease in infants” “Donor milk in milk banks is safe and healthy” “When I don’t have enough breast milk, it is better to use donor milk instead of formula to feed my baby” “Donor milk in a milk bank may carry viruses and spread disease” “Donor milk should be used widely in hospitalized infants who cannot be breastfed, if it is possible” “Donor milk can treat newborns who weigh less than normal” “I think mothers should be rewarded for donating their milk” “After pasteurization, the nutrients in milk are all destroyed, so it is better to feed baby with formula”	5-point Likert (from strongly agree to strongly disagree)
Subjective norms about DHM and HMBs	“My husband’s opinion on donating milk to the milk bank is important to me” “I will not donate my breast milk to the milk bank if my husband disagrees” “Opinions of people around me like my mother, family, friends etc. on donating milk are important to me” “I will not donate my milk to the milk bank if people around me (like my mother, family, friends etc.) disagree” “Milk donation and using donor milk have ethical issues in Islam” “God considers milk donation as a virtue and admirable action” “If I want to donate my milk, my family will support me”	5-point Likert (from strongly agree to strongly disagree)
Perceived behavioral control in milk donation	“I feel donating my milk will decrease my milk supply which is needed for my own baby” “It costs me a lot to donate my milk” “I can provide equipment for milk donation such as a container for storing milk, breast pump (if needed)” “I think I can be a milk donor” “If my husband or family are against donating milk, I can convince them” “I can express my breast milk correctly” “I can provide storage conditions for expressed milk”	5-point Likert (from always to never)
Intention to donate milk	“I am going to donate my milk to a milk bank within the next six months” “I am going to identify the milk banks where I live” “I am going to contact a milk bank within the next six months” “I am going to identify the nearest route to the milk bank” “I am going to undergo a pre-donation blood test” “I am going to inform other breastfeeding mothers about milk banks” “I am going to provide equipment for milk donation”	5-point Likert (from always to never)
Breastmilk donation	“I donated my breast milk in the last six months” “How many times did you donate your milk to the milk bank in the last six months?” “I will follow hygiene tips if I want to donate my breast milk”	Yes / No Number 5-point Likert (from always to never)

Theory of planned behavior assumes that individuals’ behavior is directly determined by three main components, namely: attitude, subjective norms, and perceived behavioral control [18, 19].

Behavior: the action of donating breast milk.Intention: perceived likelihood of donating breast milk.Attitude: favorable or unfavorable perceptions of donating breast milk which are determined by breastfeeding mothers’ knowledge, beliefs, and experiences.Subjective norms: beliefs about whether most people who are important to breastfeeding mothers approve or disapprove of donating breast milk.Perceived behavioral control: breastfeeding mothers’ perceptions of the ease or difficulty of donating breast milk.

The reliability of questions will be checked for internal consistency (Cronbach’s alpha) and the content validity of the questionnaire will be assessed by both qualitative and quantitative methods. In the qualitative method, ten experts in breastfeeding and the health promotion field will assess questioners. The experts include Faculty members of the Midwifery and Reproductive Health Department and neonatologists of Tehran University of Medical Sciences, and, after receiving their opinions, any required modification will be made. In the quantitative method, content validity index (CVI) and content validity ratio (CVR) will be measured. For face validity we will ask ten breastfeeding mothers to provide feedback on the clarity of the questionnaire and based on their opinions some essential clarification will be made.

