### Intervention design

Following baseline data collection, the intervention group will start receiving 60-minute weekly educational intervention based on TPB components for four weeks (Table 1).

**Table 1 Tab1:** The content of the educational sessions based on the theory of planned behavior

Session	Main purpose	Educational materials	Educational methods and time schedule
1	Improving breastfeeding mothers’ knowledge and attitudes toward DHM and HMB	• PowerPoint presentation • Booklet (including contents of all sessions) • Pamphlet of the first session	1) Introducing presenter and participants and explaining study aims (10 min) 2) Giving information on importance and background of breast milk donation and HMBs (40 min) 3) Question and answer (10 min)
2	Addressing the role of subjective norms in breast milk donation	• PowerPoint presentation • Pamphlet of the second session	1) Reviewing previous session (5 min) 2) Giving information related to Islamic laws of milk donation (15 min) 3) Presenter will use the psychodrama method. In this method two volunteer breastfeeding mothers role-play problems and release their intense emotions in regard to milk donation, then the presenter will guide their subjective norms [26] (30 min) 4) Question and answer (10 min)
3	Addressing the role of perceived behavioral control in breast milk donation behavior	• PowerPoint presentation • Pamphlet of the third session • Video	1) Reviewing previous session (5 min) 2) Giving information on requirements for breast milk donation, indication and contraindication of breast milk donation, process and cost of HMBs and current status of HMBs in Tehran (40 min) 3) Screening a video which shows how a HMB works (5 min) 4) Question and answer (10 min)
4	Addressing the behavioral intention and explaining how to implement the behavior of donating breast milk	• PowerPoint • Pamphlet of the fourth session • Video • Breast pump	1) Reviewing previous session (5 min) 2) Giving information on breast milk expression (10 min) 3) Showing how to express breast milk by hand and breast pump (25 min) 4) Showing videos of successful breast milk expression (10 min) 5) Question and answer (10 min)

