### Data collection

The questionnaire will be uploaded to Porsline, a well-known online survey platform in Iran, to create a link for the questionnaire. Participants can use their mobile phones to open the link and fill out the questionnaire. A baseline assessment will be conducted prior to the intervention for both the intervention and control groups. In order to assess the immediate and long-term effects of the intervention prospectively, the first follow up assessment will be conducted immediately after the intervention, and the final one will be conducted 12 weeks later. Our primary outcomes are the number of mothers who have donated their breast milk and changes that have happened in breastfeeding mothers’ knowledge, attitudes, subjective norms, perceived behavioral control about DHM and intention to donate milk. Our secondary outcomes are the associations of behavioral determinants and social demographic variables with milk donation.

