### Statistical analysis

We will use descriptive analysis to report baseline characteristics. In this study the Repeated ANOVA between subjects test will be used for quantitative variables which have a normal distribution, and the Friedman test will be used for quantitative variables that do not have a normal distribution. For qualitative variables, chi-square test or Fisher’s exact test will be used. The effectiveness of the intervention will be assessed using the repeated measure ANOVA test and the effect of demographic variables on milk donation behavior will be determined using a logistic regression model. Statistical analyses will be made using IBM-SPSS 22. The trial has been registered at the Iranian Registry of Clinical Trials (IRCT20230124057203N1).

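### The six-month donation item reaches back before baseline, so one earlier donation can count both as milk donation history and as the outcome, inflating that association to an unknown degree

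*Protocol article*

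**What the plan says.** In the protocol article, Table 2 (Development of the measurement tool) lists the questionnaire sections. The one on sociodemographic and perinatal characteristics begins "Age, education, milk and blood donation history, breastfeeding history, economic status, parity". No time limit is given for the donation history item. The section on breast milk donation contains "I donated my breast milk in the last six months" and the count item "How many times did you donate your milk to the milk bank in the last six months".

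The Data collection section states: "Our secondary outcomes are the associations of behavioral determinants and social demographic variables with milk donation". The Objectives section lists the relationship between sociodemographic variables and donation as a secondary objective. The Statistical analysis section says that "the effect of demographic variables on milk donation behavior will be determined using a logistic regression model". It does not list the covariates or say which assessment supplies the donation outcome.

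On timing, the Intervention design section says that after baseline "the intervention group will start receiving 60-minute weekly educational intervention based on TPB components for four weeks". The Data collection section says that "the first follow up assessment will be conducted immediately after the intervention, and the final one will be conducted 12 weeks later". The Recruitment section admits mothers up to one year after birth and does not exclude those who have already donated milk.

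**The concern.** A predictor measured at baseline should describe the mother before the outcome period starts. Here the outcome period starts before baseline. A donation made shortly before enrolment is part of the mother's donation history, and it also lies inside the six months that the follow-up item asks about. She is then a donor on both sides of the regression, even if she never donates again.

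The effect on this association has one direction. Double-counted mothers can only move the history odds ratio upward. Randomization does not protect against this, because the analysis compares mothers with and without a history, not the two arms. With about 60 mothers and probably few donors, two or three double-counted mothers could make prior donation look like a strong predictor. The Discussion section says that findings on what matters for donation are meant to guide later programs, so an artefact here could be carried forward.

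**Working it through.** The plan gives no figure of its own for this overlap, so there is none to reproduce. The check has three steps.

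**1. How far the outcome item reaches before baseline**

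Inputs: recall of six months (Table 2); a four-week program (Intervention design); follow-ups immediately after it and 12 weeks later (Data collection).

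- Six months = 365.25 / 2 / 7 = 26.1 weeks.
- First follow-up, about week 4: 26.1 − 4 = 22.1 weeks before baseline, 22.1 / 26.1 = 85% of the window.
- Final follow-up, about week 4 + 12 = 16: 26.1 − 16 = 10.1 weeks before baseline, 10.1 / 26.1 = 39% of the window.

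Other readings of the calendar do not remove the overlap. If four weekly sessions span only three weeks, the figures are 23.1 weeks (89%) and 11.1 weeks (43%). If the 12 weeks were counted from baseline, the final figure is 14.1 weeks (54%).

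**2. Inflation when history has no true effect**

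The inputs here are assumptions. Let q be the risk of a new donation after baseline, the same with and without a history. Let f be the share of mothers with a history whose donation falls inside the overlap. The recorded risk of donation is q without a history and p1 = f + (1 − f)q with one. The odds ratio is [p1/(1 − p1)] / [q/(1 − q)], and its true value is 1.

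| f | q | p1 | Odds ratio |
|---|---|---|---|
| 0 | 0.10 | 0.10 | 1.0 |
| 0.25 | 0.10 | 0.325 | 4.3 |
| 0.50 | 0.10 | 0.55 | 11 |
| 0.75 | 0.10 | 0.775 | 31 |
| 0.25 | 0.05 | 0.2875 | 7.7 |
| 0.25 | 0.20 | 0.40 | 2.7 |

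For example, with f = 0.25 and q = 0.10: (0.325/0.675) / (0.10/0.90) = 4.3. The odds ratio is infinite only at f = 1.

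**3. How few mothers it takes**

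Assume 60 mothers analysed (30 per group, the Sample size section's figure before attrition is added). Assume that every mother with a history donated inside the 10-week overlap and never again, and that 3 of the others donate after baseline.

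- Three such mothers, item as worded: 3/3 versus 3/57 recorded as donors. Fisher p = C(6,3)/C(60,3) = 20/34,220 = 0.0006. Odds ratio with 0.5 added to each cell: (3.5 × 54.5)/(0.5 × 3.5) = 109.
- The same mothers, counting only donation after baseline: 0/3 versus 3/57, p = 1.0.
- Two such mothers, item as worded: 2/2 versus 3/58, p = C(5,2)/C(60,2) = 10/1,770 = 0.006.
- No such mothers: no effect.

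**The case against.** The strongest objection is that the article never says donation history enters the model. It speaks of demographic variables, and the Table 2 section mixes these with perinatal items, awareness of milk banks and donation history. A covariate list is commonly left to the full protocol or analysis plan, and past donation is a behavior rather than plainly a demographic variable. This stands as a limit: inclusion is inferred. It is still the natural reading, because that section is where the article sets out these variables and no item is excepted.

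Second, the overlap is partial. A mother who donated after an earlier birth, or more than about 10 weeks before baseline and not since, is yes on history and no at the final assessment. For a mother enrolled less than 10 weeks after birth, donation after that birth can overlap only for that shorter time. This stands. A reader might infer that the association is wholly circular, that donation history must come out as the dominant predictor, or that complete separation will break the model. The documents support none of these. Separation on history needs every mother with a history to be recorded as a donor, and one older donation breaks it. Even in the example above, the history coefficient diverges but the other coefficients may still be estimable.

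Third, the example is a constructed worst case. No figure in the article supports 3 of 60 mothers donating in the 10 weeks before enrolment. The Background section reports 81 and 51 donors in two successive years and calls information on milk banks very limited, so there may be few such mothers or none. This stands, and it is why the size is given as unknown.

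Fourth, the baseline assessment can reveal earlier donors if the full questionnaire is used then, as the text implies. This is true, but the article does not say that the answers will be used this way.

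Finally, the root is the recall window, and dropping the predictor leaves the outcome contaminated. This is correct, and it sets the order of the remedies below.

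**Conclusion.** The concern holds in a limited form. As worded, the donation item counts donations made up to about 10 weeks before baseline at the final assessment and about 22 weeks at the first follow-up. Nothing in the article stops such a donation from also counting as donation history. If history is among the predictors, its association with donation is biased upward wherever the overlap occurs.

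The calendar figures rest on the article's own schedule. The size of the bias does not: it depends on how many enrolled mothers donated shortly before baseline, which the article does not give. The effect runs from nothing, if none did, to a nominally significant artefact if two or three of about 60 did under the worst-case assumptions above. The issue touches a secondary analysis and is minor, but the change is nearly free.

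**What to change.** Define the outcome of this regression as donation since baseline. The cleaner route is to word the yes/no and count items at both follow-ups as donation since the start of the study, which brings the overlap to 0 weeks. The alternative is to use the baseline answers to identify earlier donations. A mother who answers no at baseline and yes at follow-up donated after baseline. A mother who answers yes at both remains ambiguous unless the donations are dated.

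If neither is done, leave milk donation history out of the predictor set and report it descriptively, stating that pre-baseline donations remain in the outcome for every other predictor. Blood donation history has no such overlap and can stay.

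The cost is a small change to two follow-up items and one sentence in the Statistical analysis section or, on the fallback, the loss of prior milk donation as a reported predictor. The primary outcomes include the number of mothers who have donated ("Our primary outcomes are the number of mothers who have donated their breast milk"). If that number is taken from the same item, the rewording also removes pre-baseline donations from it.

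### The donation items look back six months, but the final assessment is about 16 weeks after baseline, so donations from about the last 10 weeks before baseline can count as primary outcome events

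*Protocol article*

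**What the plan says.** All references are to the protocol article.

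- **Outcome.** Data collection opens its outcome list with "Our primary outcomes are the number of mothers who have donated their breast milk". It gives no period for the donation and no restriction to new donors.
- **Items.** Development of the measurement tool describes a 46-item questionnaire, which is the only data source described. Under breast milk donation, Table 2 prints a yes/no item, "I donated my breast milk in the last six months", and a count item, "How many times did you donate your milk to the milk bank in the last six months".
- **Timing.** Intervention design states: "Following baseline data collection, the intervention group will start receiving" a "60-minute weekly educational intervention based on TPB components for four weeks". Data collection adds that "the first follow up assessment will be conducted immediately after the intervention, and the final one will be conducted 12 weeks later".
- **Who may enter.** Recruitment admits breastfeeding mothers up to one year after birth. Earlier or current milk donation is not among the exclusions. Table 2 records milk donation history as a background characteristic.
- **Analysis.** Statistical analysis names the chi-square or Fisher's exact test for qualitative variables and a logistic model for demographic effects on donation. Neither is tied to donation status at baseline.

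**The concern.** The main objective is the effect of the program on donation to milk banks, so the outcome should count donations that the program could have caused. A recall period longer than the time since baseline also picks up donations that happened before any session. The article prints the wording of the items and the visit schedule in full, so the mismatch lies in what is stated and not in detail left out of a condensed text.

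Events from before the program should fall about equally in both arms on average. They raise both proportions, shrink the difference between them and cost power. With four centers per arm and probably few donors, an uneven spread of earlier donors by chance could also move the comparison in either direction. Once the data are collected, the date of a donation cannot be recovered from these items.

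**Working it through.** **Inputs.** Recall window of six months (Table 2); four-week program starting after baseline (Intervention design); follow-ups immediately after the program and 12 weeks later (Data collection); eight centers, four per arm (Setting); 33 mothers per arm, 30 after the planned attrition (Sample size). The article gives no donation rate for either arm.

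**The plan's own figure.** The only computed figure is the sample size, and the point does not depend on it. (1.96 + 1.64)² × (3.21² + 3.17²) / 3² = 29.3, which rounds up to 30, and 30 + 3 = 33, as stated.

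**Overlap of the window with the time before baseline.** Six months is about 26 weeks. The first follow-up is at about week 4 and the final one at about week 4 + 12 = 16.

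| Assessment | Weeks since baseline | Window before baseline | Share of window |
|---|---|---|---|
| First follow-up | 4 | 26 − 4 = 22 weeks | 22/26 = 85% |
| Final follow-up | 16 | 26 − 16 = 10 weeks | 10/26 = 38% |

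Other readings of the schedule do not remove the overlap. Counting three weeks from first to last session puts the final visit at week 15, with an overlap of 11 weeks. Counting the 12 weeks from baseline gives 14 weeks.

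**What the answers can and cannot separate.** Assume that the donation items are also asked at baseline, where the window runs from week −26 to week 0. The final window runs from week −10 to week 16.

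- No at baseline and yes at the final visit: the donation was after baseline.
- Yes at baseline and yes at the final visit: either she donated after baseline, or she donated only between weeks −10 and 0. The yes/no item cannot tell these apart.
- Final count minus baseline count: donations in weeks −10 to 0 cancel, but those in weeks −26 to −10 are subtracted although the final count never included them. The result is the post-baseline count minus those earlier donations, and it can even be negative.

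**Illustration of dilution (all rates assumed).** Let p be the proportion donating after baseline and q the proportion who donated in the overlapping weeks, independent of p and equal in both arms. The observed proportion is 1 − (1 − p)(1 − q), so the difference between arms is multiplied by (1 − q). Take p = 5% and 30% with 30 per arm. Power is for a two-sided 5% test of two proportions by normal approximation, ignoring clustering.

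| q | Control | Intervention | Difference | Power |
|---|---|---|---|---|
| 0% | 5.0% | 30.0% | 25.0 points | 73% |
| 3% | 7.9% | 32.1% | 24.3 points | 66% |
| 5% | 9.8% | 33.5% | 23.8 points | 61% |
| 10% | 14.5% | 37.0% | 22.5 points | 51% |

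**Illustration of small counts (assumed counts).** Fisher's exact test, two-sided, 33 per arm: 0 against 5 gives p = 0.053; 0 against 6 gives p = 0.024; 1 against 6 gives p = 0.105. One donor with a pre-baseline donation in either arm can move such a result across 5%.

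**The case against.** **Much of the problem can be recovered.** Both groups are assessed at baseline and donation history is recorded. If the same item is asked then, its window covers all of the pre-baseline time in both follow-up windows, so new donors among mothers who had not donated can be identified. This stands. What remains ambiguous is the group reporting donation at baseline, and the article states no rule for them. Such a rule might be in a fuller document, but it could not supply dates that the items do not collect.

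**The number affected may be very small.** The Background reports 81 and 51 donors in two years at one Iranian milk bank and describes information for mothers as scarce. Among 66 mothers, the number who donated in the 10 weeks before baseline could be zero. This also stands. The power and Fisher figures are illustrations, and the Fisher counts sit near the 5% threshold by choice. They show that small counts are fragile, not that the window will cause a wrong result.

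**The 85% may not bear on the main comparison.** The article does not say that the first follow-up defines the donation outcome, so the 38% at the final visit is the more relevant figure.

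**Stronger readings that a reader might infer.** One is that any earlier donation gives a yes at every assessment. It does not: a mother whose last donation was 11 to 26 weeks before baseline answers yes at baseline and no at the final visit. Another is that the forward-looking item "I am going to donate my milk to a milk bank within the next six months" is also at fault because donation is observed for a shorter time. Intention and donation items share a six-month horizon, and the association between them is a secondary outcome. A shorter intention horizon would be a preference, not the repair of an error.

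**Conclusion.** The point holds within limits. Followed as written, the donation outcome at the final assessment includes donations from about the last 10 weeks before baseline, and at the first follow-up from about 22 weeks before it. This follows from the printed wording and schedule, and it holds on every reading of the schedule that was tried.

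The expected consequence is dilution. Bias in either direction would need earlier donors to be unevenly spread over the eight centers by chance. A reader might infer that the comparison is invalid or that a false positive is likely; the document supports neither, because randomization balances earlier donors in expectation and no pre-baseline donation rate is given. Under the assumed rates above, power falls from 73% to between 66% and 51% when 3% to 10% of mothers donated in the overlapping weeks. If none did, nothing is lost. The change is still worth making before data collection, because it concerns the first-named primary outcome and is nearly free.

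**What to change.** 1. At both follow-ups, ask whether the mother has donated since her baseline assessment, with that date shown, and how many times since then. The part of the recall period before baseline is then zero at both visits.
2. Keep the six-month wording at baseline only, as a measure of earlier donation.
3. Define the outcome in Data collection as any donation reported after baseline up to the final assessment.

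The intention items can stay as they are.

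**Cost.** Two items of an online questionnaire are reworded and one sentence is added to the outcome definition. The validity and reliability checks in Development of the measurement tool are still planned, so the new wording can go through them. The follow-up items will differ from the baseline item, so the donation answers can no longer be read as one repeated measure; with the outcome defined as donation after baseline, that is not needed.
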